## Material and methods

### Study design

This is a single-center prospective cohort study. The study period is from March 2022 to February 2025. 524 patients will participate in the study. The participants are divided into the experimental (4sb first branch and 12a anterior lymphadenectomy) or control groups (traditional 4sb and 12a lymphadenectomy). After providing informed consent, the participants will be assigned for surgical treatment by the surgeon to either the experimental or control group at a 1:1 ratio. If the patients in the experimental group are found to have positive 4sb and 12a LNs during preoperative imaging examination or during the operation, they will be included in the control group for traditional lymphadenectomy. Figure 1 is a schematic diagram of the study process.

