### Primary outcome

The primary outcome is the 12a lymph node metastatic rate. The 12a lymph node metastatic rate is equal to the number of patients with 12a LNM divided by the total number of patients enrolled.

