### Sample size

The sample size was calculated using PASS 11.0 software. The 12a lymph node metastatic rate was used as the main result in the sample size calculation. This study assumes that the 12a lymph node metastatic rate in the experimental group is not inferior to the control group. According to published literature (9), the 12a lymph node metastatic rate of the control group is estimated at 9.1%. Combined with clinical practice, the non-inferiority threshold is set to −7.4%. The size of the two groups of patients was determined with a 1:1 design, setting a significance level of *α* = 0.025 (unilateral), power at 80%, and loss to follow-up at 10%. We expect 524 patients to be registered, with 262 patients in each group.

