## Discussion

LNM is an important factor affecting the 5-year OS rate of gastric cancer patients. Therefore, the prognostic value of D2 lymphadenectomy in gastric cancer needs to be further improved (10). Saito (11) found that in 239 cases of lower-third gastric cancer undergoing D2 lymphadenectomy, the lymph node metastatic rate in the 4sb group was 2.2%, which was related to LNs invasion and advanced gastric cancer. Shu (12) found that the metastasis rate of 12a LNs was 2.67% (11/413), which was related to tumor location, depth of tumor invasion and LNs stage. For patients with advanced gastric cancer (stages III/IV) located in the lower third of the stomach, the metastasis rate of 12a LNs increased to 10.7% (11/103). The recurrence-free survival rate and OS rate of patients with 12a LNM were significantly worse. Other studies have shown that the metastasis rate of 12a LNs is 1.7%–20% and it may be one of the most important factors affecting prognosis (7, 9, 10, 13–15). Therefore, accurate lymphadenectomy plays a positive role in the prognosis. However, the scope of 4sb and 12a LND in D2 lymphadenectomy is not clear. Lin (16) found that the unqualified rate of lymphadenectomy in 948 cases of laparoscopic total gastrectomy was 51.9%, and it gradually decreased with accumulated surgical experience. It is believed that the main reason for the unqualified LNs failure is the failure to dissect LNs at specific locations during the operation. Among them, the failure rate of the 12a LNs was higher (33.44%), and the No.4 LNs were lower (9.39%). This shows that a standardized and clear range of lymphadenectomy is significantly helpful for clinicians treating gastric cancer and undertaking complete D2 lymphadenectomy. However, there are few studies on the cleaning range of 4sb and 12a.

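### Moving experimental patients with apparently positive nodes into the control group ties group membership to an imperfect correlate of the primary outcome and biases the 12a comparison

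*Protocol article*

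**What the plan says.** Under Study design, patients who have consented are "assigned for surgical treatment by the surgeon to either the experimental or control group at a 1:1 ratio". A transfer rule follows: "If the patients in the experimental group are found to have positive 4sb and 12a LNs", whether "during preoperative imaging examination or during the operation, they will be included in the control group for traditional lymphadenectomy". No rule moves patients the other way.

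Under Primary outcome, the 12a metastatic rate is "equal to the number of patients with 12a LNM divided by the total number of patients enrolled". Sample size makes this the tested quantity, on the premise that "the 12a lymph node metastatic rate in the experimental group is not inferior to the control group". It assumes a control rate of 9.1%, a margin of -7.4%, one-sided alpha of 0.025, 80% power and 10% loss, giving 262 per group.

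Nothing in the article keeps a transferred patient in the original group for analysis. The Conclusion section concedes possible selection bias in general terms and does not mention this mechanism.

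**The concern.** The finding that triggers the transfer, nodes that look positive on imaging or at operation, is a correlate of the event counted as the primary outcome. Suspected positivity therefore decides the group in which the outcome is counted. Each correctly recognised case leaves the experimental numerator and enters the control numerator, so a difference appears even if the two dissections would find exactly the same disease.

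Two conclusions are at stake. A negative margin on this outcome means that a lower experimental rate counts as worse, so the artefact pushes towards failing non-inferiority. Survival moves the other way. The Discussion reports, for one cited series, that "The recurrence-free survival rate and OS rate of patients with 12a LNM were significantly worse". Loading such patients into control flatters the reduced dissection on disease-free and overall survival, which are secondary outcomes.

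**Working it through.** **The plan's own figure.** n per group = 2 × 0.091 × 0.909 × (1.960 + 0.842)² / 0.074² = 237.1, or 238. Then 238 × 1.10 = 262 per group, 524 in total. The stated size reproduces, so the sample size is not at fault. After 10% loss, 262 × 0.9 = 236 per group remain.

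**Model of the transfer.** Inputs are p = 9.1% in both groups and a margin of -7.4 points (both from Sample size), and N = 236 per group. The share f of 12a-positive experimental patients recognised and moved is an assumption. Only true positives move at this stage.

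- Moved: m = N × p × f
- Experimental rate = (Np − m)/(N − m)
- Control rate = (Np + m)/(N + m)
- Power = Φ[(0.074 + difference)/SE − 1.96], with the unpooled SE

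For f = 25%: m = 236 × 0.091 × 0.25 = 5.37. Experimental = 16.11/230.63 = 7.0%; control = 26.85/241.37 = 11.1%; difference = -4.1 points. SE = 0.0263, and Φ(0.0326/0.0263 − 1.96) = 24%.

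| f | Experimental | Control | Difference (points) | Power |
|---|---|---|---|---|
| 0% | 9.1% | 9.1% | 0.0 | 80% |
| 5% | 8.7% | 9.5% | -0.8 | 70% |
| 10% | 8.3% | 9.9% | -1.7 | 58% |
| 25% | 7.0% | 11.1% | -4.1 | 24% |
| 50% | 4.8% | 13.1% | -8.3 | 1% |

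The expected rates do not depend on N. The artefact alone reaches 7.4 points at f of about 45%.

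**Both stations or either.** The rule names 4sb and 12a nodes together. If both must be positive, the 2.2% 4sb rate cited in the Discussion bounds the transfers: f is at most 0.022/0.091 = 24%. That gives about -4.0 points and power of about 26%. Larger f applies only if either station suffices. The 2.2% and 9.1% come from different cited series, so the cap is approximate.

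**False-positive transfers.** If 5% of node-negative experimental patients are also moved (starting from 262 per group), the difference shrinks from -4.1 to -3.3 points at f = 25%, and from -8.3 to -7.5 at f = 50%. The direction holds as long as positives are moved at a higher rate than negatives.

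**Dilution when patients stay as assigned.** Suppose the reduced dissection truly yields 1.7% against 9.1%, exactly on the margin, and every switched positive is detected. The as-assigned experimental rate is then 9.1% × f + 1.7% × (1 − f), which is 1.7%, 2.4%, 3.6% and 5.4% at f = 0, 10%, 25% and 50%. Simulated at 236 per group (lower 95% Wald limit above -7.4 points), false non-inferiority is about 4%, 7%, 15% and 35%.

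**The case against.** **Suspicion is not pathology.** The trigger is what imaging or the surgeon sees. The outcome is final histology, with micrometastasis counted as positive, and much of that is unlikely to be visible at surgery. A reader might infer that membership is defined by the outcome itself; the article supports only dependence on an imperfect correlate. This stands. With f unknown, the damage could be modest, as the 5% row shows.

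**Large shifts may be out of reach.** A reader might infer that the artefact by itself exceeds the margin. That needs f of about 45%, which the both-stations reading excludes. The wording allows either reading.

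**No false success on the stated scale.** With a -7.4% margin the bias makes the claim harder to reach. The primary harm is lost power, not a spurious positive result. This also stands.

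**Complications.** It is tempting to add that the transfer makes the reduced dissection look safer. The supporting statement in the Discussion concerns recurrence-free and overall survival only; nothing in the article links 12a positivity to the listed vascular, biliary or pancreatic complications. No such claim is made here.

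**Cohort design and missing plan.** The article concedes selection bias, the flow chart is not shown, and analysis sets are often left to an analysis plan. But this is a stated rule rather than a silence: its plain sense puts the patient in the control group, beyond describing the operation received. A general caveat does not excuse a specific, avoidable mechanism.

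**Conclusion.** The point holds in this form. The one-way transfer lowers the experimental 12a rate and raises the control rate when the true rates are equal. Under the narrow reading the artefact can reach about -4.0 points, more than half the margin, with power near 26%. Under the broad reading it can be larger. Even f = 10% costs about 22 points of power (80% to 58%). The bias opposes non-inferiority on the primary outcome and favours the experimental group on survival.

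The sizes rest on equal true rates of 9.1%, an assumed f and transfers that are true positives; false-positive transfers shrink the gap.

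**What to change.** Leave the surgical switch unchanged. In Study design, replace the wording that places the patient in the control group with a statement that the patient receives traditional lymphadenectomy but stays in the originally assigned group for analysis. State whether the trigger needs both stations or either. In Primary outcome, make the denominator for each group all patients assigned to it. Record the original assignment and any switch in the EDC as they occur.

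Because keeping switched patients dilutes the contrast and can favour non-inferiority, report the as-operated analysis alongside rather than as a minor sensitivity check. Report switched patients separately, and claim non-inferiority only if the two analyses agree. State that the as-assigned result concerns the strategy of reduced dissection unless nodes look positive, which differs from a direct comparison of the two dissections, and that it does not remove bias from surgeon-chosen assignment.

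The cost is a few sentences and two data fields, with no extra patients. The as-assigned analysis alone restores an expected difference of zero and the planned 80% power when true rates are equal. The agreement rule has a price: the as-operated analysis still carries the artefact, so the chance of a claim cannot exceed the power in the table for the f that occurs.

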**Figure 1 F1:**
[figure not shown]
Research process and flow chart. LN, lymph node.

### Inclusion and exclusion criteria

Participants need to meet the following inclusion criteria: (I) gastroscopy biopsy pathologically diagnosed as gastric cancer, with clinical stage cT_2−4_N_−/+_M_0_ by abdominal enhanced computed tomography (CT) and ultrasound endoscopy in selected cases, and tumor location in the lower third of the stomach; (II) completion of laparoscopic distal gastric surgery with D2 lymphadenectomy, with or without conversion to laparotomy; (III) age 18–75 years, with no sex restrictions; (IV) cardiopulmonary function that can tolerate radical gastric cancer surgery; (V) ability to conform to the study protocol and sign the informed consent form; (VI) complete case information.

Patients that meet any of the following criteria are excluded from this study: (I) distant metastases found before or during the operation, and radical gastrectomy is not possible; (II) inability to tolerate anesthesia or surgery or refusal of surgery; (III) cerebrovascular injury or severe heart disease that have occurred within the past six months; (IV) a history of epilepsy, central nervous system disease or mental illness that inhibits cooperation with the study; (V) other diseases that seriously affect survival time; (VI) organ transplantation requiring immunosuppressive therapy; (VII) pregnancy or lactation; and (VIII) enrollment in other clinical study.

### Participating surgeons

The surgeon's proficiency and experience in radical gastric cancer surgery with D2 lymphadenectomy have been found to affect the number of LNs dissected, postoperative recovery time, and postoperative complications (8). A meta-analysis has shown that if surgeons can perform 40 operations alone, they will be able to independently manage any issues encountered during the operation and ensure the operational standards and safety (8). The study medical team will be composed of two experienced surgeons and several experienced nurses, who will be responsible for performing operative and postoperative medical therapy. The two surgeons each completed at least 60 cases of laparoscopic radical gastric distal surgery with D2 lymphadenectomy.

### Primary outcome

The primary outcome is the 12a lymph node metastatic rate. The 12a lymph node metastatic rate is equal to the number of patients with 12a LNM divided by the total number of patients enrolled.

### Secondary outcomes

The secondary outcome has four parts: pathology data, efficacy index, safety index, and follow-up data. The pathology data comprises the 4sb lymph node metastatic rate, the number of 4sb LNs dissected, the number of 12a LNs dissected, and tumor pathological staging. The efficacy evaluation index comprises operation time, intraoperative blood loss, and postoperative recovery status (time to get out of bed, time to pass gas, time to liquid food intake, time to semi-liquid food intake, and postoperative hospital stay). The safety evaluation index comprises complications and mortality ≤30 days after surgery. Intraoperative complications include injuries of the hepatic artery, common bile duct, portal vein, spleen and pancreas. Postoperative complications include biliary fistula, delayed hepatic artery and portal vein hemorrhage, pancreatic fistula, and other pancreatic injury-related complications. Follow-up data comprises 3-year or 5-year disease-free survival and OS.

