## Introduction

Over the last few years, gastric cancer has ranked fifth in morbidity and fourth in mortality among all cancers globally (1). In 2020, the number of new cases and deaths from gastric cancer in China were 478,000 and 375,000 respectively, accounting for 43.9% and 48.6% of the global new cases and deaths from gastric cancer (2). The prognosis of gastric cancer is poor and the 5-year overall survival (OS) rate is only 35.9% in China (3). Lymph node metastasis (LNM) is the main metastasis of gastric cancer. Therefore, strict implementation of intraoperative lymphadenectomy is essential. According to the European Society of Medical Oncology (ESMO), National Cancer Comprehensive Network (NCCN), and Japanese Gastric Cancer Association (JGCA), D2 lymphadenectomy is considered as the standard treatment for gastric cancer. However, the extent of 4sb and 12a lymph node dissection (LND) is undefinable according to these guidelines (4–6), it tends to be based more on the surgeon's personal understanding and experience.

Adequate lymphadenectomy contributes to the radical cure of tumors and improves the prognosis. Concurrently, it improves the accuracy of postoperative pathological results and guides patients' postoperative treatment. However, A study has shown that excessive lymphadenectomy is associated with higher postoperative mortality (7). Therefore, lymphadenectomy should be controlled within an appropriate range. According to the guidelines (4–6), the scope of 4sb LND is along the left gastroepiploic artery (LGA), including the root, and the scope of 12a LND is along the proper hepatic artery (PHA), and needs to expose the anterior wall of the portal vein.

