The advantage of the traditional lymphadenectomy is that it thoroughly cleans the regional lymph nodes (LNs). However, there are important blood vessels around the 4sb and 12a LNs, such as the splenic artery and portal vein. The risk of vascular damage is higher, the operation is difficult, and the operation time is long. Patients with advanced lower third gastric cancer have a low rate of 4sb and 12a LNM, and the prognosis is poor. Therefore, we designed a new cleaning range. We divided the 4sb LNs into two parts, namely those at the root of the LGA and the peripheral LNs of the first branch. 12a LNs were divided into two parts, namely the anterior and posterior peripheral LNs of the PHA. According to the patient's condition, we will take the 4sb LND area as the first branch LNs of the LGA, saving those at the root, and take the 12a LNs in the anterior area of the PHA, saving those in the posterior area, in some patients. The purpose is to simplify the operation, shorten the operation time, reduce the surgical complications, and speed up the recovery of the patient while obtaining the same radical cure effect. However, the efficacy and safety of this new technique is still unclear.

Since the scope of 4sb and 12a LND is not uniform nationally and internationally and there are few studies on the effectiveness and safety of different anatomical scopes, clinical study on the scope of 4sb and 12a LND is necessary. Therefore, we designed this experiment to compare the pathology, safety, efficacy, and prognosis of the new and traditional methods of 4sb and 12a lymphadenectomy to provide a new, alternative lymphadenectomy for patients with gastric cancer.

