**Figure 4 F4:**
[figure not shown]
Schematic diagram of the scope of 12a lymph node dissection. The yellow area is the experimental group, and the yellow plus purple area is the control group.

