### Control group

We take the 4sb LNs at the first branch and the root of the LGA and take 12a LNs in the anterior and posterior areas of the PHA. LNs in the two areas will be pathologically tested separately. The two groups of LNs will be separated and removed by the surgeon during the operation, rather than trimmed from the whole *ex vivo* pathological specimen.

The scope of 4sb LND is as follows: we choose to cut off the LGA at the root of the LGA originating from the splenic artery, and then sweep along the greater curvature to the LGA and the right gastroepiploic artery interchange (Figure 3).

The scope of 12a LND is as follows: posterior border is the anterior side of the portal vein. The remaining borders are the same as the experimental group (Figure 4).

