### Statistical analysis

The normally distributed data will be expressed as mean ± standard deviation, and independent sample t-test will be used for groups differences. The non-normally distributed data will be expressed by a median, and the Mann–Whitney U test will be used for groups differences. The count data will be described as frequency and percentage and Fisher's exact test will be used for groups differences. The survival curve will be analyzed with the use of Kaplan–Meier, and the log-rank test will be used to evaluate groups differences. The Cox proportional hazards model will be used to evaluate the hazard ratio. *P* < 0.05 is set as the significance level.

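### Whole-station 4sb and 12a node counts are compared between nested dissection fields, so the test cannot show whether the shared field was cleared equally well; stage is affected only in its nodal part, and in few patients

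*Protocol article*

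**What the plan says.** The Secondary outcomes section lists "the number of 4sb LNs dissected, the number of 12a LNs dissected, and tumor pathological staging" without limiting the counts to any part of a station. The Introduction gives the aim as to "compare the pathology, safety, efficacy, and prognosis of the new and traditional methods". The Statistical analysis section gives generic rules by data type. Continuous data get a t-test if normal; otherwise "the Mann–Whitney U test will be used for groups differences". For frequencies, "Fisher's exact test will be used for groups differences".

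The Experimental group section takes only the first-branch part of 4sb and the part of 12a in front of the proper hepatic artery. The Control group section takes both of these plus the 4sb root and the posterior 12a part. The Figure 4 caption confirms the nesting: "The yellow area is the experimental group, and the yellow plus purple area is the control group". The Figure 3 caption says the same for 4sb.

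On specimens, the Control group section says "LNs in the two areas will be pathologically tested separately". The same sentence stands in the Experimental group section. The Data collection section lists node numbers and metastasis rate by station (4sb, 12a), with no sub-area item.

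**The concern.** A node count can answer two questions: how much tissue each technique removes, and how thoroughly a given area was cleared. The first is settled by the definition of the two fields. The second is the useful quality check, because the surgeon assigns patients to groups and the Participating surgeons section itself treats the number of nodes dissected as depending on surgeon proficiency. A whole-station test mixes the two, so a lower count in the experimental group says nothing by itself about dissection quality.

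Stage has a related but smaller problem. The Introduction says of adequate lymphadenectomy that "it improves the accuracy of postoperative pathological results". Metastases in the root or posterior nodes can be found only in patients who have those areas removed, so the N category is ascertained differently in the two groups. A lower recorded stage in the experimental group could be partly under-detection.

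**Working it through.** **The plan's own figure.** Inputs from the Sample size section: 12a rate 9.1%, margin 7.4 points in size, one-sided α 0.025, power 80%, 1:1, loss 10%. Equal true rates are assumed.

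n = (1.960 + 0.842)² × 2 × 0.091 × 0.909 / 0.074² = 237.2, so 238 per group. 238 × 1.1 = 261.8, so 262 per group and 524 in total. The stated size is reproduced. It concerns the primary outcome and is used here only for the group size (238 evaluable).

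**Node counts: what the test can identify.** Let μ be the control mean per station, s the share of nodes lying in the extra area, and r the experimental group's retrieval in the shared field relative to control.

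- Control mean = μ
- Experimental mean = μ(1 − s)r
- Ratio of totals = (1 − s)r

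With equal retrieval (r = 1) the expected deficit is sμ, which is above zero whenever s is. The totals cannot separate s from r. A ratio of 0.70 arises from s = 0.30 with r = 1, and equally from s = 0.10 with r = 0.70/0.90 = 0.78, which is markedly poorer clearance. On the shared field alone the ratio is r. The built-in difference is then zero under equal retrieval, and the test returns to its nominal 5%.

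**Node counts: how often the built-in deficit is significant.** The documents give neither μ nor s, so both are assumptions: μ of 1, 2 or 4, s from 10% to 50%, negative binomial counts with shape 2, r = 1, 238 per group, two-sided 0.05. There were 600 simulated trials per cell (Monte Carlo standard error at most √(0.25/600) = 2 points). Mann–Whitney rejection rates:

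| Share s | μ = 1 | μ = 2 | μ = 4 |
|---|---|---|---|
| 10% | 14% | 20% | 23% |
| 20% | 40% | 58% | 72% |
| 30% | 77% | 91% | 99% |
| 50% | 100% | 100% | 100% |

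The t-test gives similar or slightly higher rates.

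**Stage.** Depth of invasion does not depend on which nodes are removed, so only N can shift, and only in patients with positive root or posterior nodes. The ceiling adds the 12a rate of 9.1% (Sample size) to the 4sb rate of 2.2% (Discussion, a cited series). It supposes that every such patient is positive in the extra area, that none is counted twice, and that the category always changes: 9.1% + 2.2% = 11.3%, and 0.113 × 262 = 29.6, about 30 patients per group.

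Power to detect a shift in a stage category held by 30% or 50% of patients (assumed), 238 per group, counting rejections in the expected direction only:

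| Shift (points) | 30% category | 50% category |
|---|---|---|
| 1 | 4% | 4% |
| 3 | 11% | 10% |
| 5 | 23% | 19% |
| 11.3 (ceiling) | 82% | 70% |

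**Is the sub-area information recorded?** In the experimental group one part of each station is removed, so the sentence on separate testing can there mean only the two stations. In the control group four sub-areas are removed and the same sentence is repeated. The Introduction's division of each station into two parts makes the sub-area reading possible, and the station reading from the experimental group remains possible too. The Data collection list, which names stations only, does not settle it.

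**The case against.** Whole-station yield is a legitimate description of what each technique removes. The protocol sets no dedicated hypothesis for counts or stage, and a shared-field analysis could sit in an analysis plan that is not shown. All of that is fair, and it keeps this a low-priority point. It does not answer it, because the outcomes and tests as stated do not measure clearance of the shared field. Nor can a later analysis plan recover sub-area labels that were never recorded.

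Several stronger readings are tempting, and the documents do not support them:

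- A reader might infer that the tests are decided by the design. For counts, only the direction of the expected difference under equal retrieval is built in. Significance depends on an unknown share, and better or worse retrieval in the shared field also moves the total. For stage the inference fails: depth of invasion is untouched and power for small N shifts is low.
- A reader might take the 11.3% as the likely effect. It adds rates from different series under extreme assumptions, and the Discussion argues that metastasis around the portal vein is rarer still than 12a metastasis overall.
- A reader might infer that the like-for-like data are already collected. The ambiguous sentence and the station-level data list leave that open.
- A reader might infer that the survival comparison is biased through stage. The Statistical analysis section names no Cox covariates, so this is conjecture.
- A reader might expect recomputed stage to make the groups comparable. Surgeon assignment, and the Study design rule that moves experimental patients found node-positive into control, also shift stage. Removing extra-area nodes from the control count leaves both in place.

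**Conclusion.** The point stands in a narrow form, as a cheap improvement to secondary outcomes. Whole-station counts compared across nested fields are expected to be lower in the experimental group under equal retrieval whenever the extra area holds nodes, and they cannot show whether first-branch 4sb and anterior 12a were cleared equally well. The chance that this deficit is declared significant runs from 14% to about 100% over assumed shares of 10% to 50%. That range rests on assumed means and dispersion, since the documents give no node counts.

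For stage, the difference in ascertainment is real but confined to N. It is capped at about 11% of patients and is probably much smaller. The same nesting also bears on the primary 12a metastatic rate, where it matters more; that is a separate question from the one settled here.

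**What to change.** 1. In the Control group and Data collection sections, state that control-group nodes are labelled and recorded by sub-area: 4sb first branch and root, 12a anterior and posterior. State what the two separately tested areas are.
2. Make the between-group count comparison on the shared field only (first-branch 4sb, anterior 12a). Report whole-station totals and the control group's extra-area yield descriptively.
3. Report control-group stage with and without root and posterior nodes, as a within-control estimate of under-ascertainment. In the between-group comparison, give the shared-field stage alongside the full stage.
4. State that none of this removes imbalance from surgeon assignment or from moving node-positive experimental patients to control. Because that move enriches the control group, the within-control estimate should not be read as the amount missed in the experimental group.

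The cost is minor labelling and data entry plus a few extra analyses. The sample size does not change. The labelling should be settled promptly, because sub-area origin cannot be reconstructed for specimens already processed without it.
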